#### 1.1.2. Hypotheses

Ten sessions of “SR-MRehab: Un colegio emocionante” involving VR will have the same effects as the standard program on the improvement of self-regulation.

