### 2.2. Procedure and Enrollment

The implementation of the program covers the period from September 2020 to May 2021, divided into six stages: recruitment, pre-evaluation, allocation, intervention, post-evaluation and follow-up at 6 months. The initial stage corresponds to the acceptance by the management of the centers, and the subsequent invitation to the participants, by sending a letter to the parents/legal guardians, which contains an informative document of the characteristics of the project and the corresponding informed consent to participate in it. Children will be randomly assigned through the online randomization program. The type of allocation to each group will be simple randomization. The recruitment and study procedure are shown in Figure 1.

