### 2.4. Statistical Analysis

#### 2.4.1. Sample Size

According to the results of the study by Negut, Jurma and David [35], who evaluated the attention in children with ADHD using an AULA VR (virtual reality classroom) system, the minimum standardized difference (d/s, where d = difference between neurotypical and clinical groups; s = standard deviation of the neurotypical group) that could be considered clinically relevant is one point. According to this value, for a bilateral contrast with α = 0.05, and a power of 1-β = 0.90, the initially estimated sample size is 21 children. Taking into account the possible losses during the evaluation, the sample size will be increased by 20%, thus, the estimated final sample size is 26 children with neurodevelopmental disorders.

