#### 2.4.2. Data Analysis Plan

A descriptive analysis will be carried out for all the variables in the study. The qualitative variables will be described with absolute frequencies and percentages for each of their categories, and quantitative variables with mean, standard deviation (DE), maximum and minimum values, as well as median and interquartile range, where appropriate. The corresponding 95% confidence intervals (ICs) will be calculated. The normality of the continuous variables will be verified using graphical methods and normality tests.

The Chi-square test will be used to study the statistical significance of the differences between proportions. To study the statistical significance of the differences between means, different tests, questionnaire scores, completion time and number of errors of each virtual task throughout the different sessions, the following tests will be used depending on whether or not the variables to be compared show normality: Student’s t test, Mann–Whitney U-test, ANOVA or Kruskal–Wallis test. Furthermore, the effect size of the changes observed will also be calculated. The analysis of the association between two quantitative variables will be performed, using Pearson’s or Spearman’s correlation coefficient, depending on whether or not the variables show normality.

If necessary, generalized linear regression models will be used to adjust the results for any confounding covariate that shows significant baseline differences between the groups and a correlation with the result. For the hypothesis testing, a significance level of 5% will be assumed (*p* < 0.05). All statistical analyses will be carried out using the IBM SPSS software (version 24, IBM Corporation, New York, NY, USA).

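### A normality check on the trial's own data chooses between a mean-based and a rank-based test for every outcome, so the effect measure for the two primary scores is not fixed in advance.

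*Protocol article*

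**What the plan says.** Section 2.4.2 (Data Analysis Plan) states: "The normality of the continuous variables will be verified using graphical methods and normality tests". For comparing means, test and questionnaire scores, times and errors it continues: "the following tests will be used depending on whether or not the variables to be compared show normality", and lists "Student’s t test, Mann–Whitney U-test, ANOVA or Kruskal–Wallis test". Pearson or Spearman correlation is chosen in the same way. The level is set by "For the hypothesis testing, a significance level of 5% will be assumed". No outcome is exempt and no default test is named. 95% confidence intervals appear only in the descriptive paragraph, and the effect size of observed changes is promised without naming the measure.

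Section 2.2.4 names two primary measures: Affect Recognition errors (0 to 79) and the Theory of Mind score (0 to 28). Table 1 schedules both at baseline, immediately after the intervention and at 24 weeks. Section 2.4.1 sizes the trial on a standardized difference and says the smallest one "that could be considered clinically relevant is one point". Section 1.1.2 expects that the virtual-reality program "will have the same effects as the standard program on the improvement of self-regulation".

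**The concern.** The t test and the Mann-Whitney test do not address the same quantity. The first compares means. The second compares the ordering of scores, and its p-value gives no interval for a difference in means. When the data pick the test, the trial's question is settled only after the outcomes are in. One primary score could be reported as a mean difference and the other as a rank comparison, and the same score could change scale between the end of the program and 24 weeks.

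Three features make this matter here. The sample size assumes a mean difference. The hypothesis of equal effects can be judged only from an estimated between-arm difference and its interval, since a non-significant p-value from either test does not show equality. And both primary scores are bounded, one of them an error count, so some skewness or a ceiling is plausible and the switch would be in real use.

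**Working it through.** **Inputs from the protocol article.** Two-sided alpha 0.05, power 0.90, standardized difference 1.0, 21 children raised by 20% to 26 (section 2.4.1); two groups by simple randomization (section 2.2); two primary scores at two assessments after baseline (section 2.2.4, Table 1).

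**Assumptions.** The article gives no outcome distributions, allocation ratio or named normality test. I take 1:1 allocation, Shapiro-Wilk at 0.05 in each arm, and the rank test if either arm fails. Shapes are normal and gamma with shape k, whose skewness is 2/√k: k = 4 gives 1 and k = 2 gives 1.41.

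**Step 1: the plan's own figure.** n per arm = 2(z₀.₉₇₅ + z₀.₉₀)²/d² = 2(1.960 + 1.282)²/1² ≈ 21.01. Then 21 × 1.2 = 25.2, rounded up to 26. So 21 and 26 are reproduced by a mean-difference formula, which confirms the effect measure behind the design. They come out as per-arm numbers while the text reads as totals. That is a separate matter, so both readings are carried below.

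**Step 2: how often the rank test is chosen** (simulation).

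| Children per arm | Normal | Skewness 1 | Skewness 1.4 |
|---|---|---|---|
| 13 (26 in total) | about 10% | 33% | about 55% |
| 10 (26 in total, after 20% loss) | 10% | 26% | 43% |
| 26 (26 per arm) | 10% | 62% | 90% |

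**Step 3: mixed scales.** Two primary scores at two assessments give four comparisons. If each is switched independently with probability p, the chance that they do not all use the same test is 1 − p⁴ − (1 − p)⁴:
- p = 0.096: 0.33
- p = 0.33: 0.79
- p = 0.54: 0.87

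Scores from the same child are correlated, so independence is a simplification.

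**Step 4: how often the rule changes the decision.** It departs from a fixed t test only when the check fails and the two tests also fall on opposite sides of 0.05. At 13 per arm and a true difference of 0.5 to 1 SD this happens in about 1% of trials (normal), 3 to 6% (skewness 1) and 6 to 8% (skewness 1.4).

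**Step 5: error rate and power.** Under no difference the two-stage rule rejects in 4.6 to 5.6% of trials at 10 to 13 per arm. Power at 13 per arm and 1 SD, in the order t, Mann-Whitney, two-stage:
- normal: 0.688, 0.640, 0.687
- skewness 1: 0.690, 0.700, 0.717

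**The case against.** The strongest reply is that the rule does little measurable damage. Its type I error stays near 5%, it loses no noticeable power against the t test, and it seldom reverses a decision. All of that stands, and the point does not rest on error inflation.

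Four stronger readings are tempting but not supported:

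- **The test is picked almost at random.** This roughly fits moderate skewness. For normal data the t test is kept in about 90% of trials, and for strong skewness the rank test is chosen in most.
- **The conclusion is at stake in 6 to 11% of trials.** That is how often the two tests disagree on the same data at 0.5 to 1 SD. The rule acts on a disagreement only when the check has also failed, so the relevant figures are those of step 4. Taking whichever test is significant would reject in 5.4 to 6.2% of null trials, but the article does not allow that.
- **Student's t loses its level because "The type of allocation to each group will be simple randomization".** Rates of 7.3 to 11.0% need a 10:16 or 9:17 split, SDs differing 1.5- to 2-fold, and the smaller arm being the more variable one. Either arm is equally likely to be the smaller. Averaged over the splits that simple randomization produces, the rate is 5.2% (SD ratio 1.5) or 5.7% (ratio 2). Nothing in the article points to unequal variances.
- **The analyst could steer the result.** Section 2.3 blinds the data manager, who runs the analyses, to the randomization. Steering towards one arm is therefore difficult, though the effect measure still depends on the data.

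The choice of normality test, its threshold and how plot and test are reconciled can fairly be left to a fuller document. The data-driven rule cannot be excused that way, because the article states it and a fuller plan that follows it would inherit it. The article also does not say that the check is repeated at each assessment. That is a natural reading of a rule applied to the variables being compared, and nothing in the text rules it out.

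**Conclusion.** The point holds as one about the effect measure. Section 2.4.2 leaves it open whether each primary score is compared by means or by ranks, and no between-arm interval is assured under either branch. The design calculation is in means and the hypothesis of equal effects needs an interval.

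The effect on significance is modest: about 1% to 8% of decisions changed relative to a fixed t test at 13 per arm, with type I error close to nominal. These figures depend on the assumed shapes and on Shapiro-Wilk per arm. If 26 is per arm, the rank test is chosen more often under skewness (62% and 90%), so the instability remains. The change should be made, but the rule does not by itself invalidate the trial.

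**What to change.** Remove the normality check as a means of choosing the test. For each of the two primary scores, specify now the between-arm difference in means with its 95% CI from a linear model adjusted for the baseline score, in the same form immediately after the intervention and at 24 weeks. State the rank test as a sensitivity analysis and use normality plots for description only. Robust standard errors are optional, but the decision to use them should be fixed in advance. There should be no clause that changes the method if skewness is seen, since that would bring the switch back.

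The cost is wording only, because the baseline scores are already collected. Under strong skewness a mean-based test gives up some power against the rank test: about 69% against 76% at 1 SD with skewness 1.4, 13 per arm, unadjusted. Baseline adjustment can more than repay this. With normal data, power at 1 SD rises from about 69% to 78–92% if the correlation between baseline and outcome is 0.5 to 0.7, which is an assumption.

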## 2. Materials and Methods 

### 2.1. Study Design and Participants

“SR-MRehab: un colegio emocionante” is a randomized controlled trial; a non-immersive virtual reality system that will be conducted using the MRehab tool [40,41]. Children will be recruited from several schools of Granada (Spain) and they will be randomly allocated to two groups: experimental or control group. An assessment will be conducted before and after the intervention and 24 weeks after the end of the intervention process. The experimental group will receive the intervention using virtual reality. The control group will receive the intervention through a standard self-regulation program. Both interventions will be performed once a week for a total of 10 sessions (50-min sessions per day). The inclusion criteria establish that the participants must: (1) have special educational needs; (2) show oral comprehension, with the capacity to fix the gaze; (3) be able to pay attention to verbal and visual instructions; and (4) pay sustained attention for at least four minutes. The exclusion criteria are: (1) severe motor disability; (2) children with major behavioral problems, such as self-harm; and (3) children with high abilities. Initially, all students of this center with special educational needs will be invited.

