The same evaluation will be carried out immediately after finishing the program. In addition, the acceptability of the technology will be evaluated with the children at the end of each session and at the end of the whole program. A combination of methods will be used to assess acceptability [47]. Firstly, in each session, each activity will be evaluated using a Smileyometer, which is a visual analog scale with a coding based on a 5-point Likert scale (Horrible = 1; Great = 5). In addition, at the end of the program, the method “*This or That*” will be used, using five questions, for example: ‘What part of the program did you enjoy the most?’, ‘What game would you like to have at home?’ To check the long-term effects of the program, a follow-up will be carried out at 6 months, in which the emotional regulation and executive functioning of the participants will be re-assessed.

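### Covariates are adjusted for only after a significant baseline difference, so the baseline score of each outcome will almost never be used, at a cost in precision that could be large in a trial of 26 children

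*Protocol article*

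**What the plan says.** Section 2.4.2 compares groups with "Student’s t test, Mann–Whitney U-test, ANOVA or Kruskal–Wallis test", and "the following tests will be used depending on whether or not the variables to be compared show normality". Regression is a fallback for when it is judged needed, "to adjust the results for any confounding covariate that shows significant baseline differences between the groups and a correlation with the result". A covariate must therefore pass two conditions: a significant baseline difference and a correlation with the outcome. The baseline score of the outcome is not named, and no other route into the model is given for it. The one mention of change is that "the effect size of the changes observed will also be calculated".

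The baseline scores will exist. Section 2.1 states that "An assessment will be conducted before and after the intervention and 24 weeks after the end of the intervention process", section 2.2.2 that "The same evaluation will be carried out immediately after finishing the program", and Table 1 schedules each test and questionnaire at baseline, post-intervention and 24 weeks. Both primary outcomes, the NEPSY-II Affect Recognition and Theory of Mind subtests, are among them. Table 1 also lists age.

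**The concern.** In a randomised comparison a baseline difference between arms arises by chance. Testing it says nothing about whether the covariate predicts the outcome, and prediction is what determines the gain from adjustment. A significance trigger therefore discards the covariate in nearly all trials, including those where it would help most. The earlier score on the same test is usually the strongest predictor available. Age is a natural second covariate, because section 2.2.4 describes the primary outcomes by score ranges (0 to 79 errors, 0 to 28 points) and the children are 6 to 11 years old.

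What is at stake is precision. The stated hypothesis is that the two programmes have the same effects. A needlessly wide interval makes a non-significant difference more likely, and that could be misread as support for the hypothesis.

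**Working it through.** **The plan's own figure.** Section 2.4.1 states that "for a bilateral contrast with α = 0.05, and a power of 1-β = 0.90, the initially estimated sample size is 21 children", for a standardised difference of 1. For two means, n per arm = 2(1.960 + 1.282)² / 1² = 21.01. So 21 is reproduced, but as a number per arm; 21 × 1.2 = 25.2, rounded up to 26. The text does not say per arm and reads as a total. Both readings are carried below.

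**Inputs.** From the documents: difference 1 SD, two-sided α = 0.05, two groups. Assumed: 1:1 split, no losses, and r = 0.3 to 0.8, since the documents give no correlation.

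**How often the rule fires.** A test at 5% of a covariate balanced by randomisation is significant in about 5% of trials. Requiring a correlation with the outcome as well can only lower this. Simulating both conditions gave about 2 to 5%, depending on r.

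**Standard errors in SD units, n per arm.**
- Unadjusted: √(2/n)
- ANCOVA: √(2/n) × √(1 − r²)
- Change score: √(2/n) × √(2(1 − r))

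With n = 13, √(2/13) = 0.392. Power is from the noncentral t with noncentrality 1/SE, on 24 degrees of freedom (23 for ANCOVA).

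| r | Unadjusted SE; power | ANCOVA SE; power | Change-score SE; power |
|---|---|---|---|
| 0.3 | 0.392; 0.69 | 0.374; 0.73 | 0.464; 0.54 |
| 0.5 | 0.392; 0.69 | 0.340; 0.81 | 0.392; 0.69 |
| 0.7 | 0.392; 0.69 | 0.280; 0.93 | 0.304; 0.88 |
| 0.8 | 0.392; 0.69 | 0.235; 0.98 | 0.248; 0.97 |

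With 21 per arm, unadjusted power is 0.89; ANCOVA gives 0.91, 0.95, 0.99 and over 0.99. Whatever n is, the interval width shrinks by √(1 − r²), that is to about 95%, 87%, 71% and 60% of the unadjusted width.

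**The conditional rule itself.** Simulation, 13 per arm, 6,000 trials per case:

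| r | Power unadjusted | Power, plan's rule | Power, ANCOVA always | Type I error, plan's rule |
|---|---|---|---|---|
| 0.5 | 0.70 | 0.69 | 0.79 | 0.040 |
| 0.7 | 0.69 | 0.70 | 0.92 | 0.036 |

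The rule behaves like no adjustment. Simulated ANCOVA power is one or two points below the formula, which ignores chance baseline imbalance. With simple randomisation of 26 children, where arm sizes vary, the plan's rule gives 0.66 against 0.77 for ANCOVA at r = 0.5, and 0.67 against 0.90 at r = 0.7.

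**The case against.** The strongest reply is that the plan may use baseline after all. Section 2.2.4 says participants are expected to change on each outcome, and section 2.4.2 promises effect sizes of changes. A t test on change scores would fit the listed methods and needs no trigger. Under that reading the loss against ANCOVA at r = 0.7 is only about 4 points (0.88 against 0.93). This stands as a possibility. However, no change-score test is named, and below r = 0.5 such a test does worse than ignoring baseline.

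Two further limits stand. At r = 0.3 the gain is small (0.69 to 0.73), and if 21 is per arm, power is already near the planned 0.90. Compared with plain unadjusted testing, the conditional rule costs essentially nothing; the loss is relative to always adjusting.

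A reader might infer more than the text supports:
- *That the three visits will be pooled, or pre and post compared, as independent samples, giving wrong standard errors.* The listed rank tests are for independent groups, and no paired rank test appears, so the suspicion is understandable. But no section says this. Comparing the arms separately at each visit with these tests is valid.
- *That the two-step rule raises false positives.* It does not; the error is slightly below 5%.
- *That choosing the test by normality does measurable harm here.* Nothing in the documents allows that to be sized, and this point does not rest on it.

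**Conclusion.** The point holds in this form: section 2.4.2 fixes an adjustment rule that will almost never be triggered, and so, unless change scores are tested, leaves out the baseline score that the trial collects anyway. This is a stated rule, not a detail left to a fuller document. On the total-of-26 reading, always adjusting raises power at a difference of 1 SD from about 0.69 to between 0.73 and 0.98 for r from 0.3 to 0.8. On the 21-per-arm reading the rise is from about 0.89 to between 0.91 and over 0.99. The size depends on r, which is assumed, and on the planning difference of 1, which is taken over from the plan without endorsing it. The benefit of adding age was not computed. The defect is lost efficiency, not invalidity: the planned analysis keeps its type I error at or slightly below 5%. The wording should be changed, and the change is cheap.

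**What to change.** Replace the conditional-adjustment sentence in section 2.4.2 with: *Each primary and secondary score at post-intervention and at 24 weeks will be compared between arms by ANCOVA (or an equivalent mixed model over the two post-baseline visits), with the baseline score of the same test, and age, as prespecified covariates, regardless of any baseline difference.* Remove baseline significance testing as the trigger for adjustment.

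One check is needed when applying this. The Auditory Attention and Cognitive Flexibility subtest, a secondary outcome in section 2.2.4, is not in Table 1, so its baseline assessment should be confirmed.

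The cost is one or two degrees of freedom per model and a change of wording. No further data, visits or children are needed.

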### 2.5. Ethical Approval, Ethical Considerations and Dissemination

The study protocol was approved by the Research Ethics Committee of the University of Granada (registration number 1018/CEIH/2019), and this study was registered at ClinicalTrial.gov (under identification no. NCT04418921). This study respects the principles established in international and national legislation in the field of biomedicine, biotechnology and bioethics, as well as all the rights derived from the protection of personal data. All investigators will have updated their report of criminal offences, as required by the current legislation for working with children in Spain.

The entire educational community will be informed about the project verbally and in writing. Participation in the project will be voluntary and all participants will give their written informed consent and will not receive any incentive to participate in the study. Weekly, the parents, teachers and the educational community, in general, will be informed about the progress of the project, through the school blog. The results of this study will be presented at international scientific meetings and will be disseminated in scientific journals. In addition, this study will be the subject of a Master’s thesis (TFM) and a final degree project (TFG).

In our study, the results of a traditional educational program for the development of self-regulation (control group) and a program designed using our non-immersive virtual reality system (experimental group) will be compared. The effectiveness of the treatment will be evaluated through direct tests with the children and questionnaires about their participation and performance in their activities of daily living and in the classroom. The children will be assessed before and immediately after the intervention. Many interventions do not address emotional regulation and cognitive regulation together. The proposed protocol will evaluate the effectiveness of the proposed virtual reality tool “SR-MRehab: Un colegio emocionante”, versus standard program without VR.

At the time of submission of this manuscript (5 May 2020), the project has been presented to the educational community of “Parque de las Infantas” Infant and Primary School. The project is expected to start in October 2020. One possible limitation of this study is the type of sampling, which is convenience, voluntary and non-probabilistic.

Another potential limitation is related to the fact that the improvement found in emotional regulation and executive functioning might not only result from the program itself, but also from the natural development that occurs in the months in which the intervention is carried out. However, these changes should be reduced, due to the scattering of the 10 intervention sessions established over the study period of six months.

